### Methods in analysis to handle protocol non-adherence and any statistical methods to handle missing data {20c}

For the intention-to-treat analysis, we will use GLMMs. We will also perform secondary analyses excluding those not considered completers and those who started any other mental health treatment during the intervention period.

### Plans to give access to the full protocol, participant-level data and statistical code {31c}

Any data required to support the protocol can be supplied on request. The datasets analysed during the current study are available from the corresponding author on reasonable request.

## Oversight and monitoring

### Composition of the coordinating centre and trial steering committee {5d}

The trial coordinating centre comprises the principal investigator and trial managers. They will monitor the progress of the trial (including the recruitment of participants and attrition) and ensure adherence to its protocol. They will report any adverse events to the trial steering committee and research ethics committee.

The senior investigator of our group chairs the trial steering committee. He will therefore be responsible for decisions regarding the continuation, modification or termination of the study. Modifications will be implemented only after approval by the research ethics committee and adjustment of the clinical trial registry.

### Composition of the data monitoring committee, its role and reporting structure {21a}

This protocol has been approved by the local research ethics committee, which did not recommend the creation of a data monitoring committee.

### Adverse event reporting and harms {22}

The risk for participants is expected to be minimal, because the intervention is non-invasive. However, we will monitor participants to identify any potential side effects of the intervention, including increased symptomatology and emergence of suicidal ideation. In the clinical assessments (interviews with the guardians and the children/adolescents), the blinded assessor will collect data on symptomatology (through the use of the RCADS-25-P, ARI, SDQ impact supplement, CGI-S and CGI-I), emergence of suicidal ideation (through the use of the MFQ-SI) and disruption of family dynamics (through the use of the PedsQL family impact module). The blinded assessor will also collect data on any other form of mental health treatment that the family seeks between T0 and T2, including psychotherapy with other providers or psychopharmacological treatment.

If by the end of treatment the assessor identifies a significant level of symptomatology, the child/adolescent will be referred to continue the treatment within the Brazilian public health care system. One of the child psychiatrists on the team will evaluate the child/adolescent if necessary.

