### Outcomes {12}

The primary outcome measure will be a change in the symptoms of anxiety and depression, as determined by the RCADS-25-P and RCADS-25-C [28, 29], between study entry (T0) and 1–3 days after the end of the intervention (T1, after five sessions of psychotherapy, five weeks of access to the psychoeducational videos, or both). The RCADS-25-P and RCADS-25-C will be completed by an independent clinician blinded to the allocation, on the basis of interviews (through videoconference or telephone call) with the guardians and the children/adolescents, respectively. The response variables will be the continuous T-scores for the three RCADS-25 domains (total, depression and anxiety).

Secondary outcomes will include the following: a change in the symptoms of anxiety and depression at follow-up; global functioning, assessed by the Clinical Global Impression (CGI) scale [41] and the Children’s Global Assessment Scale (CGAS) [30, 42]; the impact of mental health symptomatology, as determined with the Strengths and Difficulties Questionnaire (SDQ) impact supplement [43]; changes in irritability; emotional problems; environmental changes, as determined by passive smartphone data collection; the level of parental satisfaction with the telepsychotherapy sessions; and the potential harm (emergence of suicidal ideation and worsening of the quality of family relationships).

The blinded assessor will evaluate the difference between the anxiety and depressive symptomatology observed at T0 and that observed at follow-up (T2, 30 days after the last psychotherapy session, for the intervention group, or 30 days after the last video is made available, for the active control group) in an interview with the guardian and the child/adolescent, using the RCADS-25-P and RCADS-25-C.

The blinded assessor will evaluate the global functioning of the participants in interviews with the guardian and the child/adolescent (through videoconference or telephone call). The CGI-Severity (CGI-S) and CGAS scores obtained at T0 will be compared with those obtained at T1 and with those obtained at T2. Scores on the CGI-S range from 1 to 7, higher scores corresponding to greater symptom intensity. Scores on the CGAS range from 0 to 100, higher scores indicating better functionality. The CGI-Improvement (CGI-I) scores will be assessed at T1 and T2. Scores on the CGI-I range from 1 (“very much improved”) to 7 (“very much worse”).

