The impact of the mental health symptomatology on the lives of the children/adolescents will be compared between T0 and T1, as well as between T0 and T2, by using the SDQ impact supplement [43], the score on which ranges from 0 to 10, higher scores indicating greater distress and impairment. The SDQ impact supplement will be completed by the blinded assessor in an interview with the guardian and the child/adolescent (through videoconference or telephone call).

Irritability is a quite common psychopathological trait in youth and is related to many disorders, including depression and anxiety [44]. Therefore, we will evaluate the changes in child/adolescent irritability, as reported by the parents/guardians, between T0 and T1, as well as between T0 and T2. To that end, the blinded assessor will apply the parent-report Affective Reactivity Index (ARI), an index created to assess irritability [45], in an interview (by videoconference or telephone call).

Participants ≥ 12 years of age with access to a smartphone will complete an ecological momentary assessment (EMA), which is a brief in-the-moment assessment of emotions, mood, stress and anxiety. Each of those participants will receive a notification on their smartphone to answer a series of questions intended to reflect their current state (“Right now, I feel…”), with a 7-point Likert scale ranging from 0 (“not at all”) to 7 (“very much”). The EMA employs the experience sampling method (ESM) schedule [46], which consists of 17 questions and takes 3 min or less to complete. The ESM schedule will be delivered at four random times every day, within four 3-h blocks from 9:00 to 21:00, for six consecutive days in the week prior to the trial period and in the week after its end.

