Participants ≥ 12 years of age with access to a smartphone will be asked to install an application designed to passively collect data from the smartphone sensors—the passive remote measurement technology (pRMT) application from the Remote Assessment of Disease and Relapse (RADAR)-base platform [47]. The pRMT application will run in the background, requiring minimal input from participants, and will use the smartphone sensors to collect data on the following: ambient noise and light; relative GPS location (i.e. the distance travelled, rather than absolute coordinates or precise geographical location); the number of Bluetooth-enabled devices nearby; the duration of calls; the number of text messages and emails; the time spent using the smartphone; the time spent on social media; and battery life. Passive data collection will take place from T0 to T2. The aim of these measures is to determine whether parameters such as physical activity (estimated by the distance travelled) and proximity to other people (estimated by analysing Bluetooth connectivity with other smartphones) might be related to changes in anxiety and depressive symptomatology and whether those parameters show any improvement after the trial.

To assess the level of parental satisfaction with the telepsychotherapy sessions (intervention group only), parents will be asked to complete an adapted version of the Telemedicine Satisfaction Questionnaire (TSQ) [48].

Potential harms were defined as the emergence of suicidal ideation and worsening of the quality of family relationships. As previously mentioned, we will use the parent-report four-item MFQ-SI to assess suicidal ideation in the last 2 weeks [31, 32], comparing T1 with T2. The MFQ-SI will be completed by the blinded assessor in an interview with the guardian (through videoconference or telephone call). To identify worsening of the quality of family relationships in the last 2 weeks, we will use the family relationship subscale of the family impact module of the Pediatric Quality of Life Inventory (PedsQL) [49]. The PedsQL will be completed by the blinded assessor in interviews with the guardian at T0, T1 and T2. The family relationship subscale of the PedsQL comprises five items, covering topics such as “lack of communication between people in my family”. For each item, there is a 5-point Likert scale (responses ranging from “never” to “almost always”).

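### Symptom worsening is monitored as a side effect but left out of the harm outcome, and the child RCADS-25 is missing from the monitoring list

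*Protocol article*

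**What the plan says.** Two sections of the protocol article deal with harm.

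- **Adverse event reporting and harms {22}** commits the team to broad monitoring: "we will monitor participants to identify any potential side effects of the intervention, including increased symptomatology and emergence of suicidal ideation". It names the symptom instruments: "through the use of the RCADS-25-P, ARI, SDQ impact supplement, CGI-S and CGI-I". The MFQ-SI is added there for suicidal ideation and the PedsQL module for family dynamics. The RCADS-25-C does not appear.
- **Outcomes {12}** lists harm among the secondary outcomes as "the potential harm (emergence of suicidal ideation and worsening of the quality of family relationships", and later repeats the definition: "Potential harms were defined as the emergence of suicidal ideation and worsening of the quality of family relationships". Both components come from the guardian. For the first, "we will use the parent-report four-item MFQ-SI to assess suicidal ideation in the last 2 weeks"; for the second, "The PedsQL will be completed by the blinded assessor in interviews with the guardian at T0, T1 and T2".

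The same Outcomes section makes both RCADS-25 forms, parent and child, the primary measure from T0 to T1 and uses both again at T2. In each case a blinded assessor completes them by interview.

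**The concern.** The article describes harm in two ways that do not match. One section names worsening symptoms as a side effect to look for. The other gives a closed definition of the harm outcome without it. An author who follows the Outcomes section when writing the results would report harm by arm without a count of participants whose anxiety or depression got worse. Yet the sections on discontinuing interventions {11b} and concomitant care {11d} both foresee that event.

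The efficacy analysis does not supply the count. Statistical methods {20a} promises mixed-model coefficients and marginal means by arm and time. A mean that falls in both arms is compatible with a minority who deteriorate. Some average fall is likely in any case, because entry requires high scores on both forms and regression to the mean will follow. With no interim analysis and no data monitoring committee, the final harm table carries most of the weight of what the trial can say about safety.

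A second, smaller mismatch is that the child form has equal standing with the parent form for eligibility and for the primary outcome, but is dropped without a stated reason where symptom worsening is monitored.

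**Working it through.** No figure in the plan bears on this point, so the check compares the two sections instrument by instrument.

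| Instrument | Source of the rating | Listed for monitoring in {22} | Part of the harm outcome in {12} |
|---|---|---|---|
| RCADS-25-P | guardian | yes, symptoms | no |
| RCADS-25-C | child | **no** | no |
| ARI | guardian | yes, symptoms | no |
| SDQ impact supplement | guardian and child interview | yes, symptoms | no |
| CGI-S | assessor, from guardian and child interviews | yes, symptoms | no |
| CGI-I | assessor, from guardian and child interviews | yes, symptoms | no |
| MFQ-SI | parent | yes, suicidal ideation | yes |
| PedsQL family relationships | guardian | yes, family dynamics | yes |

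Step 1. Is symptom worsening a side effect under {22}? Yes. The section refers to "any potential side effects of the intervention, including increased symptomatology and emergence of suicidal ideation".

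Step 2. Is it in the harm outcome under {12}? No. None of the five symptom instruments listed in {22} feeds the harm outcome. Its two components use the MFQ-SI and the PedsQL subscale.

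Step 3. Does the omission affect only child report? No. The RCADS-25-P is outside the harm outcome just as the RCADS-25-C is. The difference between informants lies in the monitoring list of {22}, not in the outcome definition.

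Step 4. Is the child absent from monitoring? No. Of the five listed symptom instruments, three (SDQ impact, CGI-S, CGI-I) use interviews with the child. Two rest on the guardian alone: the RCADS-25-P, and the ARI, for which "we will evaluate the changes in child/adolescent irritability, as reported by the parents/guardians".

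Step 5. Are the data there? Yes. Both RCADS-25 forms are completed at T0, T1 and T2, and the CGI-I is rated at T1 and T2 on a scale whose far end is marked worsening. Nothing new has to be collected.

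**The case against.** The best defence is that worsening is neither unmeasured nor unheard. CGI-I is a listed secondary outcome and rates each participant, with 7 as the worst score. The child's account reaches the CGI and SDQ impact ratings. Participants who need more care are referred, and other treatment sought between T0 and T2 is recorded. The list in {22} also omits the CGAS, which suggests an incomplete summary rather than a decision to exclude child report. Finally, an exact deterioration threshold is the kind of detail that a condensed article may leave to the full protocol or analysis plan.

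Most of this stands, and it limits the point to classification. It does not remove the mismatch, because the article does more than stay silent: it states a closed definition of harm that leaves out something it elsewhere calls a side effect. CGI-I, though measured, is not labelled as harm.

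A reader might draw four stronger conclusions, which the documents do not support.

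- *The missing child form is why child-reported worsening goes uncounted.* It is not. Section {22} sets no counting rule for any instrument, and the harm outcome leaves out parent-reported worsening as well.
- *The safety assessment rests almost wholly on the guardian.* This describes the two-item harm outcome but not the monitoring, where three of five symptom instruments include the child.
- *Guardian report is the more biased because the guardian is unblinded.* Child and guardian both attend the sessions and only the assessors are blinded, so this argument does not favour either informant.
- *A known share of deteriorations is missed.* The article gives no worsening rate, no parent-child agreement and no rule that counts harm from the parent form alone, so no percentage can be derived.

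**Conclusion.** The point holds as an inconsistency between Adverse event reporting and harms {22} and Outcomes {12}. Symptom worsening is monitored as a possible side effect but is not part of the harm outcome, whichever informant reports it. The RCADS-25-C is in addition missing from the symptom list, although it is a primary measure collected at every assessment.

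The severity is minor. Data collection, alpha, power, sample size and the primary analysis do not change. What changes is what the trial can conclude about harm: a count of deteriorated participants by arm answers a question that mean-change models cannot. The conclusion rests only on reading the two-item definition as closed, which is how both statements of it in the Outcomes section are worded. The number of participants affected cannot be estimated from the documents.

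**What to change.** Reconcile the two sections.

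1. In {22}, add the RCADS-25-C to the instruments used to monitor symptom worsening.
2. In {12}, add symptom deterioration to the harm outcome in both places where that outcome is defined.
3. Report it as number and percentage per arm at T1 and at T2, relative to T0, for the parent and child forms separately. Show the number and percentage in the CGI-I worsened categories alongside.
4. Fix the RCADS-25 threshold before analysis, in the protocol or the analysis plan, so that harm is not defined after the data are seen. It is a reporting threshold only and does not alter referral or treatment decisions.

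The cost is a wording change and one extra table; all scores are already collected. The downside is a somewhat higher reported harm rate in both arms, so the table should be read as a comparison between arms.

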### Strategies to improve adherence to interventions {11c}

The intervention sessions will be recorded on video; 10% will be randomly selected to be watched by one of the authors of the manual, to assess therapist adherence to the protocol. Each session is described in detail in the manual, helping make the intervention more homogeneous among the various therapists of the research group. All of the therapists will receive weekly supervisory sessions led by senior psychotherapists. An assessor blinded to the allocation will register the percentage of psychoeducational videos watched by the patient and guardian.

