**Fig. 1 Fig1:**
[figure not shown]
Schedule of enrolment, interventions and assessments. ARI: Affective Reactivity Index; CGAS: Children’s Global Assessment Scale; CGI-I: Clinical Global Impression-Improvement; CGI-S: Clinical Global Impression-Severity; DASS-21: 21-item Depression, Anxiety and Stress Scale; EMA: Ecological momentary assessment; MFQ-SI: Mood and Feelings Questionnaire-Suicidal Ideation; PedsQL: Pediatric Quality of Life Inventory; RCADS-25-C: 25-item version of the Revised Children’s Anxiety and Depression Scale, child report; RCADS-25-P: 25-item version of the Revised Children’s Anxiety and Depression Scale, parent report; SDQ: Strengths and Difficulties Questionnaire; TSQ: Telemedicine Satisfaction Questionnaire

Parents will complete an online form for eligibility screening and for the collection of sociodemographic data, as well as the 21-item parent-report psychopathology questionnaire Depression, Anxiety and Stress Scale (DASS-21) [50]. If their child/adolescent is considered eligible in this first assessment, a videoconference with a blinded outcome assessor will be scheduled. In this first videoconference, the eligibility criteria will be checked with the guardian and the child/adolescent. The baseline (T0) assessment will be made, confirming or correcting clinical data previously reported by the guardian at the eligibility screening. Two other videoconferences, in which similar clinical data will be collected by the blinded outcome assessor, will be scheduled for T1 and T2.

As previously mentioned, active smartphone data collection (the EMA) will be performed in the week prior to the intervention and in the week after its end, whereas passive smartphone data collection (through the pRMT application) will take place from T0 to T2. At T1, guardians in the intervention group will be asked to complete an online form comprising an adapted version of the TSQ [48].

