## Assignment of interventions: blinding

### Who will be blinded {17a}

The outcome assessor will be blinded to the group allocation. Families will be instructed not to provide the outcome assessor with any details regarding the treatment.

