### Procedure for unblinding if needed {17b}

The design of the trial is single-blind. Because only the outcome assessors will be blinded, no unblinding will occur.

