### Data management {19}

All data from the assessments and the sessions will be entered in the Research Electronic Data Capture [63], which is a secure database. The clinical data collected in the enrolment phase will be confirmed or corrected in the baseline assessment. All data, except the sociodemographic data, the TSQ score, the EMA results and the passive data, will be collected by a trained assessor.

The self-report data will be stored on the COMVC servers. The mobile smartphone sensor data will be stored on the RADAR-base platform. Both categories of data will also be backed up to Google Drive and Dropbox, and only the research team will have access to them.

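### The blinded assessor asks families about other psychotherapy in the interviews that yield the outcome ratings, an avoidable risk of unblinding mainly in the intervention arm

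*Protocol article*

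**What the plan says.** All points are from the protocol article.

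- **Who is blinded.** The trial is single-blind. Under Procedure for unblinding {17b}: "Because only the outcome assessors will be blinded, no unblinding will occur".
- **How blinding is protected.** Who will be blinded {17a} gives one measure: "Families will be instructed not to provide the outcome assessor with any details regarding the treatment".
- **Who rates the outcomes.** Outcomes {12}: "The RCADS-25-P and RCADS-25-C will be completed by an independent clinician blinded to the allocation, on the basis of interviews". The blinded assessor also scores CGI-S, CGI-I, CGAS, the SDQ impact supplement and the ARI from interviews.
- **Who asks about other treatment.** Adverse event reporting and harms {22}: "The blinded assessor will also collect data on any other form of mental health treatment that the family seeks between T0 and T2". Outside psychotherapy and drug treatment are given as examples. This directly follows the sentence that lists the scales collected in the clinical interviews.
- **What separates the arms.** Under Intervention description {11a}, the intervention arm has five weekly sessions with a psychologist plus 15 videos. The control arm has the same videos on the same schedule and no therapist.
- **What is already kept out of the interview.** Data management {19}: "All data, except the sociodemographic data, the TSQ score, the EMA results and the passive data, will be collected by a trained assessor". The satisfaction questionnaire (TSQ), used in the intervention arm only, goes by another route at T1: "guardians in the intervention group will be asked to complete an online form" (Participant timeline {13}).

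**The concern.** Families know their allocation, so blinding holds only as long as they do not reveal it. The plan asks them to keep quiet about treatment and then has the assessor open the subject of psychotherapy. A control family has no study therapist to distinguish from anyone else. An intervention family does, and a natural reply such as 'only with your psychologist' gives the arm away. Any leak from this question would therefore fall mainly on one side.

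What is at stake is the credibility of the assessor-rated comparisons. The primary RCADS-25 scores are completed by the clinician from an interview, and CGI and CGAS rest on the clinician's judgement. If a rater who learns that a child had therapy scores that child as somewhat better, the treatment difference is inflated in favour of the intervention.

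**Working it through.** **Step 1. The sections side by side.**

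| Question | What the article states |
|---|---|
| Stated safeguard | Families withhold treatment details from the assessor ({17a}) |
| Who asks about other treatment | The blinded assessor ({22}) |
| Setting | Most naturally the clinical interviews described in the preceding sentence ({22}); it is not among the items exempted from assessor collection ({19}) |
| Who rates the outcomes | The blinded assessor, by interview ({12}) |
| Arm with a trial therapist | Intervention only ({11a}) |
| Order of the question relative to the ratings | Not stated |
| Recording of any disclosure | Not stated |

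The first five rows establish the risk. The last two show only that the article does not close it. They do not show that the trial's working instructions fail to do so.

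**Step 2. The plan's own figures (Sample size {14}).** With a standardised effect of 0.41, alpha 0.05 (two-sided assumed) and 80% power, a two-sample t-test needs 94.4, rounded up to 95 per arm, or 190 in total. This matches the stated minimum. Allowing for 30% attrition gives 190 / 0.70 = 271.4, so 272; the plan enrols 280. Evaluable at that attrition: 280 × 0.70 = 196, or 98 per arm.

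**Step 3. Scale, on assumed values.** The documents give neither a disclosure rate nor a rating shift. Let *p* be the share of intervention interviews in which this question reveals the arm, over and above slips that would happen anyway, and let *s* be the shift in SD when the rater knows. Assume no corresponding leak in the control arm. Then:

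- bias *b* = *p* × *s*
- noncentrality = *b* / √(2/98) = 7*b*
- true type I error = probability that a nominal two-sided 5% t-test with 194 degrees of freedom rejects when the only difference is *b*

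| *p* | *s* (SD) | *b* (SD) | *b* / 0.41 | 7*b* | True type I error |
|---|---|---|---|---|---|
| 0.10 | 0.1 | 0.01 | 2% | 0.07 | 5.1% |
| 0.10 | 0.2 | 0.02 | 5% | 0.14 | 5.2% |
| 0.25 | 0.3 | 0.075 | 18% | 0.525 | 8.2% |
| 0.50 | 0.3 | 0.15 | 37% | 1.05 | 18.1% |
| 0.50 | 0.5 | 0.25 | 61% | 1.75 | 41.4% |

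The low end is negligible and the high end is serious. Nothing in the documents says where the trial lies. The upper end also depends strongly on the range chosen for *s*: capping it at 0.3 rather than 0.5 SD lowers the worst case from 41.4% to 18.1%.

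**The case against.** The strongest reply is that the two rules can both be kept. The instruction to families concerns the trial treatment; the harms question concerns other treatment. A family with no outside care says no in either arm, and a family with outside care names it in either arm. Any separation from the study psychologist can be made silently. This stands: a reader might infer that the sections contradict each other, and they do not. What remains is that the question raises psychotherapy with people who know their arm, and that a careless answer is revealing mainly on one side.

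Second, question order, scripts and blinding checks usually sit in assessor manuals, which an article leaves out. This also stands, so the silence is not itself the fault. The point is that the article assigns this question to the blinded assessor. The intervention-only TSQ is already kept out of the interview, which shows that a separate route exists.

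Third, a reader might add video use to the charge, since the plan says: "An assessor blinded to the allocation will register the percentage of psychoeducational videos watched by the patient and guardian". That does not hold. Both arms have the same videos, so the percentage does not identify the arm, and registering it does not have to mean asking the family, because an application log is not excluded.

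Fourth, a reader might infer that a disclosure at T1 necessarily contaminates T2. That requires the same assessor at both visits, which the article does not state.

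Finally, the RCADS-25 records symptom frequency on a fixed 4-point scale. It may leave less room for rater expectation than CGI or CGAS, which are secondary. That is a fair reason to expect a smaller shift on the primary outcome, but not none, since a clinician completes the scale.

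**Conclusion.** The concern holds as an avoidable risk of differential unblinding, arising from one question put by the one party the trial keeps blinded. The documents do not show that a leak will occur or how large it would be. On assumed disclosure rates of 10% to 50% and rating shifts of 0.1 to 0.5 SD, the bias runs from 0.01 to 0.25 SD, or 2% to 61% of the planned 0.41. These figures show scale only; it would be wrong to read the upper error rate of 41.4% as an estimate for this trial. The direction, towards the intervention, assumes that disclosure comes mainly from that arm and that informed raters expect benefit.

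A change is warranted because assessor blinding is the trial's only blinding and the remedy costs almost nothing.

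**What to change.** Amend Adverse event reporting and harms {22} so that, at T1 and T2 and in both arms, the assessor asks about other mental health treatment only after all outcome ratings have been saved: RCADS-25-P and RCADS-25-C, CGI, CGAS, SDQ impact supplement and ARI. Have the assessor record any disclosure of allocation, whenever it occurs, so that its frequency by arm can be reported.

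The alternative is to move the item to an online guardian form like the one used for the TSQ, extended to the control arm and to T2. That removes the topic from the interview, but some forms will not come back. The data are needed to define who is left out of the analyses in Methods for additional analyses {20b} and in the non-adherence section {20c}. Asking the item last keeps those data and the assessor's ability to clarify answers, so it is the preferred option. It does not undo a T1 disclosure if the same assessor also rates T2, which is a further reason to record disclosures.

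Cost: a short change to assessor instructions and form order, with no extra visits or staff. The online route would also need reminders.
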